### Objectives

This assessor-blinded randomized controlled study aims to systematically evaluate the efficacy of an add-on Ayurveda therapeutic regimen compared to conventional treatment as usual (TAU) in improving the clinical outcomes of PD.

The secondary objectives are to explore the effects of add-on Ayurveda therapy in comparison to conventional TAU on multiple physiological and functional parameters, namely cortical excitability, assessed through single (motor threshold [MT], resting cortical, and silent period [SP]) and paired pulse (short intracortical inhibition [SICI], long-interval cortical inhibition [LICI], and intracortical facilitation [ICF]) transcranial magnetic stimulation (TMS) measures; and immune parameters, including Th1/Th2/Th17/T-regulatory cell population, plasma C-reactive protein, plasma levels of Th1/Th2/Th17 pathway cytokines, and telomere length.

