### Hypothesis

This study hypothesizes that Ayurveda treatment, when integrated with standard TAU, will be safe and effective in improving clinical and cognitive outcomes in patients with idiopathic PD. It is expected that these therapies will enhance the optimal response to levodopa, potentially leading to better symptomatic control. Ayurveda interventions are hypothesized to modulate cortical excitability measures, which will correlate with improvements in both clinical and cognitive parameters. Furthermore, it is postulated that add-on Ayurveda therapies may induce a significant shift in the Th1/Th2/Th17/T regulatory cell population, along with alterations in plasma levels of pro-inflammatory cytokines and telomere length, which will further correlate with clinical, cognitive, and neurophysiological outcomes. Finally, it is anticipated that autonomic dysfunction, as measured through heart rate variability (HRV), will show significant improvement following Ayurveda interventions, aligning with overall clinical benefits observed in patients with PD.

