Safety assessments will include monitoring for treatment-emergent adverse events throughout the study period. Liver function tests, renal function tests, and complete blood count will be performed at baseline and at the end of the study (day 180) to detect any potential systemic adverse effects. For participants undergoing Basti therapy, adverse events (AEs) will be monitored during the in-patient care.

Participants in the TAU arm will continue with their dopaminergic medications. At baseline, stabilized or optimized dopaminergic doses will be recorded, and any subsequent changes during the trial will be documented along with dates and reasons. Levodopa equivalent daily dose (LEDD) will be calculated at each visit (baseline and follow-ups) using standardized conversion factors and tracked longitudinally.

All clinical and neurophysiological outcome assessments will be performed by a trained SRF with an MD (Ayurveda) qualification, and the routine assessments will be done by the neurologists involved in the study before prescribing the study TAU interventions or deciding changes in interventions. The SRF underwent a 3-month structured training program under the supervision of a neurologist and neurophysiologist to ensure competency in administering both clinical and neurophysiological assessments. The same SRF will also be responsible for data collection throughout the study to maintain consistency.

All outcome measures are evaluated using validated clinical scales and standardized laboratory instruments, as detailed in the manuscript, each with established reliability and validity. Before the commencement of data collection, all laboratory instruments and procedures will be calibrated and standardized. To promote data quality, assessors received formal training, and interrater reliability for the primary outcome measure (MDS-UPDRS Part III) will be established in at least 20% of participants.

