### Statistical Analysis

All analyses will be performed using SPSS software. The primary outcome, change in MDS-UPDRS Part III score from baseline to 24 weeks, will be analyzed using a mixed model for repeated measures with treatment, time, and treatment×time interaction as fixed effects and baseline values as covariates. LEDD will be included as a time-varying covariate to account for dopaminergic medication effects. Results will be reported as least-square mean differences with 95% CIs. The main analysis will follow a modified intention-to-treat approach including all randomized participants who receive at least one dose of the assigned intervention, whereas a per-protocol analysis will be performed as a sensitivity check on participants who complete ≥80% of scheduled therapies and medication adherence.

Missing data will be handled under the assumption of data missing at random using the mixed model for repeated measures model, which uses all available data without imputation. Additional sensitivity analyses, including multiple imputation and complete case analyses, will be performed to evaluate the robustness of results. The secondary outcomes will be analyzed using appropriate mixed or generalized linear models and interpreted as exploratory. Descriptive statistics will summarize categorical variables as frequencies and percentages, and continuous variables as mean (SD), median (IQR), and range.

Predefined subgroup analyses will explore whether treatment effects differ by baseline Hoehn and Yahr stage (≤3.0 vs >3.0), disease duration (<5 vs ≥5 y), age (<65 vs ≥65 y), baseline LEDD (≤ median vs >median), and presence of dyskinesia. Interaction terms will be tested using mixed effects models, and the results will be interpreted as exploratory. Sensitivity analyses will include assessing participants with stable dopaminergic doses (<10% LEDD change) and testing the interaction between treatment allocation and LEDD change to explore medication-dependent effects. Safety analyses will be descriptive, summarizing AEs and serious AEs by treatment group.

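### The primary model adjusts for post-randomisation LEDD, which may change with treatment, so the reported difference does not target the total effect of adding Ayurveda to usual treatment

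*Protocol article*

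**What the plan says.** The protocol article words its aim as follows: "systematically evaluate the efficacy of an add-on Ayurveda therapeutic regimen compared to conventional treatment as usual (TAU) in improving the clinical outcomes of PD" (Objectives section).

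The Statistical Analysis section specifies for the primary outcome a "mixed model for repeated measures with treatment, time, and treatment×time interaction as fixed effects and baseline values as covariates". It then adds: "LEDD will be included as a time-varying covariate to account for dopaminergic medication effects". It goes on: "Results will be reported as least-square mean differences with 95% CIs". The headline result therefore comes from the LEDD-adjusted model.

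On LEDD itself, the Outcome Measures section says: "Levodopa equivalent daily dose (LEDD) will be calculated at each visit (baseline and follow-ups) using standardized conversion factors and tracked longitudinally". Dose changes during the trial are allowed and logged with dates and reasons. On who decides them, the same section says that "the routine assessments will be done by the neurologists involved in the study before prescribing the study TAU interventions or deciding changes in interventions".

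The Hypothesis section states: "It is expected that these therapies will enhance the optimal response to levodopa, potentially leading to better symptomatic control".

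Two further LEDD analyses are planned. The first reads "Sensitivity analyses will include assessing participants with stable dopaminergic doses (<10% LEDD change"; the second tests the interaction of arm with LEDD change. Baseline LEDD appears only as a subgroup factor.

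**The concern.** A covariate measured before randomisation sharpens a treatment comparison without changing what it estimates. A covariate measured after randomisation can change it. If the arm affects LEDD, directly or by changing the symptoms to which the neurologist responds, then holding LEDD constant removes or distorts part of the effect that the trial was set up to measure. If symptom severity also drives both dose and score, the comparison at equal LEDD is confounded, so the coefficient is not a clean effect at fixed dose either.

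At stake is the primary estimate. The Sample Size section presents this trial as a basis for later confirmatory trials, so a distorted difference would carry over into their planning. No analysis in the article omits post-randomisation LEDD, so nothing planned would reveal the distortion. The stable-dose subset and the interaction test condition on the same variable, while the per-protocol, multiple-imputation and complete-case analyses address adherence and missing data.

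**Working it through.** The article gives no LEDD mean, variance, correlation or arm difference, so there is no figure of its own to reproduce on this point. The check has two parts: whether the route from arm to LEDD is open, and what adjustment does when it is.

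**1. Is the route open?**
- LEDD is calculated at each follow-up visit, and changes are allowed (Outcome Measures).
- Neurologists assess the patient before deciding on changes (Outcome Measures).
- The participant opens the allocation envelope (Assignment of Interventions). Only the outcome assessor and the data analyst are described as blinded.
- Better levodopa response and symptom control are hypothesised (Hypothesis).

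Nothing closes the route. The requirement of a stable regimen for at least 2 weeks applies before baseline only.

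**2. Illustration A: dose follows the score and has no effect on it.**

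Inputs: the baseline-to-follow-up correlation is taken as 0.60, the coefficient in the Sample Size section (that it is a pre-post correlation is an assumption). The within-arm correlation ρ between LEDD and score is assumed.

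Scale score Y and LEDD L to variance 1 within arm, with L = ρY + u and Var(u) = 1 − ρ². The arm changes Y by −δ and hence L by −ρδ. Baseline explains 0.60² = 0.36 of Y and leaves 0.64. Given arm and baseline:
- coefficient of L = 0.64ρ / (0.64ρ² + 1 − ρ²) = 0.64ρ / (1 − 0.36ρ²)
- arm coefficient = −δ × [1 − 0.64ρ² / (1 − 0.36ρ²)]

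| ρ | 0.64ρ² | 1 − 0.36ρ² | Shrinkage |
|---|---|---|---|
| 0.3 | 0.0576 | 0.9676 | 6% |
| 0.5 | 0.1600 | 0.9100 | 18% |
| 0.7 | 0.3136 | 0.8236 | 38% |

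Without baseline in the model the shrinkage would be ρ², that is 9%, 25% and 49%. The planned model contains baseline, so the smaller figures apply.

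**3. Illustration B: dose acts on the score.**

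All values are assumed; negative means benefit. A is arm, B is baseline, and U, ε and η are independent standard normal.
- Symptoms before the dose decision: S = 0.5B + U + dA
- Dose: L = 0.3B + gS + aA + 0.8ε
- Score: Y = S + bL + 0.5η, with b = −0.4

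The arm's effect on LEDD is m = gd + a. Then:
- total effect = d + bm
- LEDD-adjusted effect = d − cm, with c = g / (g² + 0.64)
- adjusted minus total = −(b + c)m

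For g = 0.5, c = 0.5 / 0.89 = 0.562. For g = 0, c = 0.

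| Case | d | a | g | m | Total | Adjusted |
|---|---|---|---|---|---|---|
| Neither arm nor symptoms affect LEDD | −0.5 | 0 | 0 | 0 | −0.50 | −0.50 |
| Dosing follows symptoms | −0.5 | 0 | 0.5 | −0.25 | −0.40 | −0.36 |
| Same, and arm lowers LEDD | −0.5 | −0.5 | 0.5 | −0.75 | −0.20 | −0.08 |
| No direct effect, arm lowers LEDD | 0 | −0.5 | 0 | −0.50 | +0.20 | 0.00 |
| Same, and dosing follows symptoms | 0 | −0.5 | 0.5 | −0.50 | +0.20 | +0.28 |

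Regressions on 400,000 simulated participants per case agreed to within 0.005. In every case with symptom-driven dosing, the adjusted value equals neither the total effect nor the direct effect d.

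**4. How the bias can nearly vanish.** Take the second case and vary b. The adjusted effect is d × (1 − 0.562 × 0.5) = 0.719d and the total is d × (1 + 0.5b).
- b = 0: 0.719 / 1.00 = 72% of the total effect
- b = −0.4: 0.719 / 0.80 = 90%
- b = −0.6: 0.719 / 0.70 = 103%

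Near b = −0.56 the two distortions cancel. That is a coincidence of values, which the design does not guarantee.

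**The case against.** **The article does not predict a change in LEDD.** This stands. The hypothesis concerns response to levodopa, not dose, and doses are to be stabilised or optimised at baseline. A reader might infer that Ayurveda is expected to lower LEDD, or that the treating neurologists are known to be unblinded. The text says neither; it leaves the neurologists' blinding status unstated. The point needs only that LEDD may respond to arm or symptoms, and the article leaves that open.

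**A reader might infer a false benefit if doses fall in Group B while scores stay equal.** The documents do not support this. Set the total effect to 0 with m = −0.5 and b = −0.4, so that d = −bm = −0.20. If dosing is not symptom-driven (c = 0), the adjusted value is −0.20, which is the genuine benefit at equal dose: a different quantity, not a false one. If dosing follows symptoms (c = 0.562), it is −(−0.4 + 0.562) × (−0.5) = +0.08, which counts against Group B. The sign cannot be foretold.

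**The inert-dose percentages overstate the problem.** Partly right. LEDD is in the model because dose is thought to act on the score, and then the bias can be small. The percentages are illustrations, not predictions.

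**An effect at equal dose may be what is wanted.** The article states no such target, and under symptom-driven dosing ordinary covariate adjustment does not deliver it.

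**The trial is exploratory, and the stable-dose subset is already a sensitivity analysis.** Both are true. The label does not make the primary estimate answer the stated objective. The second point means only that the subset's labelling needs to change.

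**Conclusion.** The point holds. The primary model conditions on a post-randomisation variable that may change with treatment, so the reported difference does not target the total effect of adding Ayurveda to usual treatment. With symptom-driven dosing it is not a valid fixed-dose effect either. Freedom from bias can be relied on only if LEDD is unaffected by arm and symptoms; otherwise it depends on chance cancellation.

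Size and direction are unknown. The shrinkage of about 6%, 18% or 38% rests on an inert dose, a baseline correlation of 0.60 and assumed within-arm correlations of 0.3, 0.5 and 0.7. When dose acts on the score, the bias can be close to nil. The case for change rests on the mismatch between objective and model, not on any one of these figures.

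**What to change.** Fit the primary model with treatment, visit, treatment-by-visit, baseline score and baseline LEDD, and without post-baseline LEDD. Report LEDD change from baseline to day 180 by arm alongside it, so that readers can see whether dosing diverged.

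Keep the time-varying-LEDD model as a supplementary analysis. Label it, the subset with less than 10% LEDD change, and the test of treatment by LEDD change as not protected by randomisation.

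The cost is a protocol amendment before unblinding, possibly a substantial one needing ethics approval under the Protocol Amendments section, and a little more analysis work. LEDD is already calculated at baseline and at every follow-up visit, no interim analysis is planned, and the data analyst is blinded, so the change can still be made cleanly. No dose or clinical rule is affected.

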### Selection of Participants

#### Inclusion Criteria

Participants eligible for the study will be those diagnosed with Idiopathic PD based on the UK Parkinson’s Disease Society Brain Bank criteria [15]. The study will include individuals in Hoehn and Yahr stages 2.5 to 4, with a disease duration of more than 3 years, experiencing severe motor fluctuations and suboptimal response to standard treatment, including dyskinesia and gait freezing. The eligible age range for participation will be 40 to 70 years. Participants must be on a stable dopaminergic regimen for ≥2 weeks before baseline.

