### Assignment of Interventions

Participants will be prescreened from the OPD and inpatient department of consultant neurologists at NIMHANS by the designated study team. Following prescreening, the principal investigator (PI) will conduct formal screening procedures and enroll eligible participants. Allocation to study arms will be performed using a computer-generated randomization sequence prepared by an independent statistician from the funding agency (CCRAS). Allocation concealment will be ensured using the sequentially numbered, opaque, sealed envelopes approach to prevent selection bias during participant enrollment. Once the patient is enrolled, the study PI shall provide the sequentially numbered envelope with the group allocation concealed inside to the participant who will open it.

The Ayurvedic interventions will be administered by the PI, who is a qualified Ayurveda physician. Standard conventional care will continue to be managed by the participant’s treating neurologist, as per routine clinical practice. However, the assessor conducting the assessments will remain blinded to group allocation to minimize bias.

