#### Group B (Conventional TAU With Add-On Ayurveda—Intervention Group)

Participants will receive Ayurveda intervention as an adjunct to the conventional treatment for a period of 180 days, comprising 3 cycles of Ayurveda therapies at 60-day intervals. The regimen is structured as follows:

Preparatory phase (*Deepana-Pachana* therapy): To enhance digestion and metabolism, participants will be administered *Chitrakadi Vati* (250 mg per tablet), 2 tablets with warm water, 3 times daily before food for a duration of 5 days.Shodhana therapy (purification phase—*Basti* [rectal administration of medicine] therapy): This includes a Yoga Basti regimen, wherein a combination of *Niruha Basti* (therapeutic decoction enema) and *Anuvasana Basti* (oil enema) will be administered in a prespecified regimen in the form of *Basti* comprising one *Sneha Basti* initially, 3 decoction *Bastis* alternately followed by 3 *Sneha Bastis,* and 1 *Sneha Basti* in the end aimed at pacifying *Vāta Dosha*.Niruha Basti: Decoction of *Erandamoola* (made with the root of *Ricinus Communis* Linn [450 mL]) administered rectally on an empty stomach as per the protocol for *Yoga Basti*.*Anuvasana Basti*: *Bala Taila* (90 mL) administered immediately after food on 5 occasions as per the protocol for *Yoga Basti*.Shamana therapy (pacificatory phase): Following purification, the participants will receive oral Ayurveda formulations for symptomatic relief and alleviation of vitiated *Vata Dosha* for 47 days in each cycle as follows:*Mashabaladi Kwatha* (decoction)—15 mL, with 2 pinches of asafoetida and rock salt administered with warm water 3 times daily.*Kalyanaka Ghrita* (medicated ghee)—20 mL, taken early in the morning on an empty stomach.The complete Ayurveda intervention regimen will be repeated thrice over the study period, with 3 cycles of 60 days each, totaling 180 days.

Usual concomitant care (if any), including physiotherapy and occupational therapy, will be permitted as part of standard management and will be recorded as concomitant therapy. However, the use of any additional Ayurvedic therapies or herbs not specified in the study protocol will be prohibited during the trial to avoid confounding effects. All concomitant medications, including any dose modifications of standard medications or rescue interventions required for symptom management, will be documented at each study visit in the case report forms.

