### Strategies for Improving the Fidelity of Care Providers and Adherence of Participants

The Ayurvedic intervention is standardized and will be administered uniformly as per the protocol. Participants will be screened for suitability before Panchakarma therapy, and the intervention will be withheld in cases of intolerance, fever, respiratory infection, or any other clinical contraindication. To ensure uniformity, all procedures will follow standard operating protocols, and participants will receive patient information leaflets detailing the interventions.

As panchakarma therapies are delivered in an inpatient or closely supervised setting by trained professionals, adherence will be monitored daily through direct supervision and treatment logs. Participants are required to maintain a compliance form to record the intake of both standard care and add-on oral Ayurvedic medications, which will be reviewed by the study team during follow-up visits. Furthermore, to promote participant retention and minimize missing data, follow-up will be reinforced through periodic telephonic contact between scheduled visits.

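### The first-dose rule for the main analysis set rests on an event after open allocation that in practice only the Ayurveda arm can fail; read literally, it excludes nobody

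*Protocol article*

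**What the plan says.** All references are to the protocol article.

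- **Main analysis set (Statistical Analysis).** The main analysis follows a "modified intention-to-treat approach including all randomized participants who receive at least one dose of the assigned intervention". The other analyses named are per-protocol (at least 80% of therapies and adherence), complete-case, multiple imputation and a stable-dopaminergic-dose subset. No analysis of all randomised participants is named. Nothing says that multiple imputation reaches beyond the modified set.
- **Control arm.** Inclusion Criteria: "Participants must be on a stable dopaminergic regimen for ≥2 weeks before baseline". Outcome Measures: "Participants in the TAU arm will continue with their dopaminergic medications".
- **Ayurveda arm.** The Group B section: "Participants will receive Ayurveda intervention as an adjunct to the conventional treatment for a period of 180 days". Each of the three cycles opens with five days of oral tablets, before the enema phase. The Intervention section defines Group B as Ayurveda given together with usual treatment.
- **Knowledge of allocation (Assignment of Interventions).** Once a patient is enrolled, "the study PI shall provide the sequentially numbered envelope with the group allocation concealed inside to the participant who will open it". Also: "The Ayurvedic interventions will be administered by the PI, who is a qualified Ayurveda physician". Only the assessor and the data analyst are described as blinded.
- **Suitability check (fidelity and adherence section).** "Participants will be screened for suitability before Panchakarma therapy, and the intervention will be withheld in cases of intolerance", among other grounds.
- **Follow-up (Harms section).** Outcome assessment ends for anyone who discontinues or deviates from the intervention protocol.

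**The concern.** A first-dose rule does little harm when failing to start cannot depend on the arm, as under double-blind conditions. Here participant and treating investigator both know the arm before the first Ayurveda dose, and only one arm has anything new to start. Dropping those who decline makes membership of Group B's analysis set depend on a choice made after allocation, with no matching exclusion under usual treatment. If never-starters differ in prognosis from the rest of Group B, the comparison picks up a difference that the treatment did not cause. None of the other named analyses is stated to restore the randomised groups, and the per-protocol set selects further on adherence.

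**Working it through.** **1. Who can fail the test?**

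| | Usual treatment | Ayurveda add-on |
|---|---|---|
| On assigned drugs at randomisation | Yes, stable for at least 2 weeks | Background drugs only |
| Anything new to start | No | Yes |
| Arm known before the first new dose | Nothing new to start | Yes, to participant and principal investigator |
| Can realistically fail the rule | No | Yes, by declining |

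This holds in practice rather than by wording. A control who took no drug at all after randomisation would also fail, but that is remote given the entry criterion.

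**2. The literal reading.** The Intervention section makes usual treatment part of Group B's assigned intervention. A Group B participant who only continues levodopa has then had a dose, the rule removes nobody, and it has no purpose. The article does not define what counts as a dose.

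**3. Size.** The plan gives no figure for never-starters, so there is none to reproduce. The Results section reports 14 discontinued of 58 enrolled (14/58 = 24.1%) without arm or timing, so this is not a count of never-starters.

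Inputs from the Sample Size section: 40 per group, SD 2.0, planned effect 1.0. Assumed: *m* = 2 or 4 of the 40 in Group B never start; they differ from starters by *k* = 0.5 or 1.0 SD; no controls are excluded; the true effect is zero.

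With *f* = *m*/40, starters' mean *R* and never-starters' mean *E*, the full-arm mean is (1 − *f*)*R* + *fE*. So *R* minus the full-arm mean is *f*(*R* − *E*), of size *fk*.

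SE in SD units = √(1/40 + 1/(40 − *m*)).

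Two-sided type I error = 1 − Φ(1.96 − *fk*/SE) + Φ(−1.96 − *fk*/SE).

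| *m* | *f* | *k* (SD) | *fk* (SD) | Points (× 2.0) | SE | Type I error |
|---|---|---|---|---|---|---|
| 2 | 0.05 | 0.5 | 0.025 | 0.05 | 0.227 | 5.1% |
| 2 | 0.05 | 1.0 | 0.05 | 0.10 | 0.227 | 5.6% |
| 4 | 0.10 | 0.5 | 0.05 | 0.10 | 0.230 | 5.5% |
| 4 | 0.10 | 1.0 | 0.10 | 0.20 | 0.230 | 7.2% |

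Against the planned 1.0 point, that is 5% to 20% of the effect, in either direction. If as many as 8 of 40 never started, the same formulas give 0.10 to 0.20 SD and 7.1% to 13.5%; nothing in the article points to that many. The calculation ignores other dropout and baseline adjustment, which would absorb part of any gap.

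**4. Would a new set definition be enough?** The primary model uses post-baseline change scores and all available data without imputation. A never-starter plausibly counts as having discontinued or deviated, so under the Harms section has no score at days 60, 120 or 180. Someone with no post-baseline score adds nothing to this model, so redefining the set alone would leave the estimate essentially unchanged.

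**The case against.** The case for leaving the rule alone has several parts.

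- **The suitability check.** A reader might infer that Group B's analysis set is also filtered by clinicians before the first dose. The article does not support this. The check is not dated relative to the oral tablets that open each cycle, and someone who fails it just before the enema phase would already have had a dose and would stay in the set. Intolerance as a ground for withholding also suggests that treatment has begun. Only outright refusal clearly leads to exclusion, and that group may be small.
- **The control side.** A reader might also infer that every control is compared with a selected part of Group B. That goes too far. A control who withdraws before day 60 has no post-baseline score and drops out of the model too. The dose rule is one-sided; effective loss from the analysis is not.
- **Surprise at allocation.** Procedures and risks are explained at consent, so the envelope reveals the arm and not what the treatment involves. This makes refusal less likely but does not rule it out.
- **Size and direction.** Both are assumed. Milder or sicker patients might decline, so the bias could favour either arm.
- **Exploratory purpose.** The trial calls itself exploratory, but Trial Design also calls it a superiority trial, and its main estimate should rest on the groups as randomised.

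These points limit the size of the problem and the claims that can be made. They do not remove it: the rule is stated, it operates after open allocation, and no named analysis undoes it.

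**Conclusion.** The point holds as a structural weakness of uncertain, probably modest, size. The rule either removes only Ayurveda-arm never-starters or, read literally, removes nobody; neither is a sound basis for the main analysis. On the assumed inputs (2 to 4 of 40, 0.5 to 1.0 SD), the distortion is 0.025 to 0.10 SD with type I error of about 5.1% to 7.2%. The article supplies neither the number of never-starters nor the sign of the difference, so it cannot be said that the rule favours Ayurveda. The rule on stopping outcome assessment matters as much as the set definition, and the two must be changed together.

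**What to change.** 1. In Statistical Analysis, define the primary set as all randomised participants with a baseline score, analysed in the arm to which they were randomised, whether or not a first dose was taken.
2. Keep the first-dose set as a sensitivity analysis, and state what counts as a dose in each arm.
3. Amend the Harms section so that outcome assessments at days 60, 120 and 180 are still sought, with consent, from participants who never start the add-on. The reason given there for stopping, the need for ON and OFF assessment, does not by itself rule this out: a never-starter can be on the same kind of background treatment as controls.
4. Report never-starters by arm, including any among the 58 already enrolled by August 2025 whose visits may have been missed.

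Cost: a protocol amendment that reverses a stated rule, a few extra visits, and possibly a slightly diluted estimate. Missed visits may not be recoverable, so an early change is worth more: recruitment was still under way in August 2025, with completion due in September 2026.

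### The stable-dose subset and the treatment-by-LEDD-change test condition on dose changes made after randomisation, so they are not reliable checks on the main result

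*Protocol article*

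**What the plan says.** The Statistical Analysis section names two sensitivity analyses about dopaminergic dose: "Sensitivity analyses will include assessing participants with stable dopaminergic doses (<10% LEDD change) and testing the interaction between treatment allocation and LEDD change". The first restricts the sample. The second is a moderator test with an exploratory purpose: "testing the interaction between treatment allocation and LEDD change to explore medication-dependent effects".

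Other sections show what LEDD change is and how it arises:

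- **Timing.** Under Outcome Measures, LEDD "will be calculated at each visit (baseline and follow-ups) using standardized conversion factors and tracked longitudinally", and "any subsequent changes during the trial will be documented along with dates and reasons". Inclusion Criteria require at least 2 weeks on a stable regimen before baseline.
- **Who decides.** Outcome Measures: "routine assessments will be done by the neurologists involved in the study before prescribing the study TAU interventions or deciding changes in interventions". The trial's own outcome assessments are done by a separate research fellow.
- **Why doses change.** The Group B section records concomitant medication, "including any dose modifications of standard medications or rescue interventions required for symptom management, will be documented at each study visit".
- **Blinding.** Only the outcome assessor (Assignment of Interventions) and the data analyst (Plans for Data Storage, Handling, and Availability) are stated to be blinded.
- **Expected effect.** Hypothesis: "It is expected that these therapies will enhance the optimal response to levodopa".

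**The concern.** A sensitivity analysis should ask the same question as the main analysis under different assumptions. Restricting to participants whose dose stayed within 10% asks about a group that is only identified during follow-up. If a participant who worsens tends to have the dose raised, that participant leaves the subset. If treatment alters how often this happens, or if a neurologist aware of allocation acts on different thresholds in the two arms, different kinds of participants leave each arm. Randomisation then no longer protects the comparison.

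The interaction test has the same weakness. LEDD change is a possible consequence of treatment and of the disease course, not a baseline characteristic, so a non-zero interaction need not mean that the treatment effect depends on medication.

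What is at stake is interpretation. A smaller difference in the stable subset could be read as a benefit explained by medication, and a similar one as confirmation. Neither reading would be secure.

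**Working it through.** **Step 1: is LEDD change post-randomisation?** Stability is required of everyone before baseline, and LEDD is recalculated at days 60, 120 and 180. A rule of less than 10% change cannot be a baseline split. The only LEDD variable in the section fixed before randomisation is the baseline-median subgroup.

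**Step 2: closed-form check.** There is no figure in the plan to reproduce, because the documents give no dose-change rate. The scale is borrowed from Sample Size (effect 1.0, SD 2.0); the rest is assumed. Let the need for a dose increase be a standard normal variable with correlation ρ to the motor change. Treatment lowers that need by d SDs, and a participant is stable if the need is below a cut-off c. With λ(x) = φ(x)/Φ(x),

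apparent benefit = true benefit − SD × ρ × [λ(c) − λ(c + d)].

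- *50% of controls stable (c = 0), ρ = 0.6, d = 0.5:* λ(0) = 0.798 and λ(0.5) = 0.509. The bias is 2 × 0.6 × 0.289 = 0.35. A true benefit of 1.0 appears as 0.65, and a true zero as about −0.35 (simulated −0.34).
- *70% of controls stable (c = 0.524), ρ = 0.3, d = 0.25:* λ = 0.497 and 0.379. The bias is 2 × 0.3 × 0.118 = 0.07.
- *Range simulated (ρ 0.3 to 0.6, d 0.25 to 0.5, 50–70% of controls stable):* 1.0 appears as 0.65 to 0.92; 0 appears as −0.07 to −0.34.
- *ρ = 0 or d = 0:* no bias.
- *Opposite sign, d = −0.5, c = 0, ρ = 0.6:* λ(−0.5) = 1.141. The bias term is 2 × 0.6 × (0.798 − 1.141) = −0.41, so a true zero appears as a benefit of 0.41. The direction depends on an unknown.

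**Step 3: three-visit simulation on the Part III scale (negative = improvement).** All inputs are assumed: between-person SD 12, individual drift to day 180 SD 5, visit noise SD 4. The dose is raised after worsening of more than 3 points (later scores −4) and lowered after improvement of more than 8 (later scores +2). In the null case, Group B is raised only after more than 6 points.

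| Dosing decision based on | Truth | Stable subset | All participants, scores after dose change set to missing |
|---|---|---|---|
| Neurologist's separate reading | −4 | −3.18 | −3.49 |
| Neurologist's separate reading | 0, unequal thresholds | +0.53 | +0.35 |
| Recorded trial score | −4 | −2.35 | −3.99 |
| Recorded trial score | 0, unequal thresholds | +1.23 | 0.01 |

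The separate-reading rows fit Outcome Measures best. There the subset loses (4 − 3.18)/4 = 20% of the effect and the alternative (4 − 3.49)/4 = 13%.

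**Step 4: the interaction test.** In the Step 2 model, the within-arm slope of outcome on LEDD change is SD × ρ. If dosing tracks outcome with ρ = 0.5 in controls and 0.2 in the treated arm, the interaction is 2 × 0.2 − 2 × 0.5 = −0.6 with no true effect modification. With equal ρ it is zero, but the treatment coefficient still shifts by SD × ρ × d = 2 × 0.5 × 0.5 = 0.5. In the Step 3 set-up with no effect and 28 per arm, the test rejects in 5.4% of trials with equal thresholds, and in 6.9% and 11.3% in two runs with unequal thresholds.

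**Step 5: precision.** Two-sample power for an effect of 1.0 with SD 2.0 is 46% at 28 per group. It is 35% if 70% are stable (19.6 per group) and 26% if 50% are (14 per group).

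**The case against.** These are supplementary analyses in a trial that calls itself exploratory. The main analysis keeps the modified intention-to-treat set, and the interaction is only meant to explore. That stands, and it limits the severity.

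Several stronger readings are tempting, and the documents do not support them:

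- *That nothing else in the plan addresses medication.* The primary model includes LEDD as a time-varying covariate, and Part III is also scored in the OFF state after 12 hours without dopaminergic medication.
- *That the subset nearly halves a real effect.* The −2.35 result needs neurologists to act on the recorded trial score. The article describes their assessments as separate from the research fellow's.
- *That most of the data would be discarded.* Under the Step 3 thresholds about 22 of 56 participants remain, but those thresholds are assumed. Step 2 supposes 50–70% of controls stable.
- *That the trial hypothesises a change in LEDD.* The Hypothesis section expects a better response to levodopa. An effect on dosing is plausible from that, but it is an inference.

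It is also fair to say that the alternative is imperfect. In the separate-reading variants it gave −3.5 to −3.7 against −3.2 to −3.5 for the subset, a modest gain.

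**Conclusion.** The point holds as one about supportive analyses. Both condition on a variable set after randomisation, on symptom grounds, by clinicians not stated to be blinded, and possibly affected by treatment. Neither can serve as reliable evidence that the main result is robust.

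The size is an illustration, not an estimate. Under assumed inputs with separate-reading dosing, −4 becomes about −3.2, and zero becomes about +0.5 when thresholds differ by arm. The bias vanishes if treatment does not affect dosing or if dosing is unrelated to outcome, and its sign can reverse.

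A reader might infer that the primary result is invalid; these two analyses do not make it so. Conditioning on time-varying LEDD in the primary model is a separate and more serious matter. Correcting that would still leave these two analyses in place.

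**What to change.** 1. Replace the stable-dose subset with an analysis of all participants in the main analysis set. Set Part III to missing at visits after the first LEDD change of 10% or more. Fit the mixed model, or use multiple imputation, with baseline and earlier Part III scores and baseline LEDD, not time-varying LEDD. Label the result as the effect had doses not changed.
2. Report LEDD change by arm as an outcome.
3. Keep the treatment-by-LEDD-change test only as descriptive, and take it off the list of sensitivity analyses. The planned treatment-by-baseline-LEDD subgroup test is a valid baseline-modifier analysis, but it does not answer the dose-change question and should not be offered as a substitute.

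The cost is wording. LEDD at each visit, the dates of dose changes, and the MDS-UPDRS at all four visits are already collected, and recruitment was still open in August 2025. State the downside in the plan: the replacement assumes missing-at-random after a dose change, gives a wider interval than an analysis using all scores, and reduces but does not remove bias when dosing follows a separate clinical reading.
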